## Background

Without intensifying efforts to improve the quality of intrapartum care, many mothers will continue to die while giving life, and the renewed promise of the Sustainable Development Goals will not be achieved [1]. It is estimated that 201,000 women died in pregnancy and childbirth in sub-Saharan Africa alone in 2015 [2]. Postpartum haemorrhage (PPH) is the most common cause of maternal mortality; 29% of maternal deaths are attributable to this complication [3]. Between 11% and 17% of women who give birth in eastern Africa experience PPH [4, 5] with at least one in 1000 women dying due to haemorrhage and 30 more suffering a severe morbidity as a result [6, 7].

Capacity building of providers to prevent, identify and treat complications is one critical element of health system strengthening. It has been increasingly recognised that training must be tailored specifically to the needs of the health workers and their work conditions [8]. Recent evidence has also demonstrated that to build capacity, competency-based training may bring the best results in terms of improving health care providers’ skills and knowledge [9]. Competency-based learning is an approach that defines individual skills or learning outcomes as a competency and defines small units of learning. Learners work on one competency at a time, which is likely to be a small component of a larger learning goal. This approach is distinct from broader courses which were historically preferred. Often such competency-based training packages also employ simulation methods to improve skills and confidence.

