### Evaluation methodology

The evaluation is based on the primary outcome of severe maternal morbidity and several secondary outcomes which include preventive actions and case management of PPH; knowledge, skills and confidence in preventing and managing PPH; and facility readiness for prevention and care of PPH (Table 1). The evaluation uses the framework proposed by Kirkpatrick to assess training interventions along the pathway of impact from reaction, learning, behaviour and results [31]. We also assess the facility readiness — the capacity of the facility in terms of trained staff, equipment and supplies — to care for women with PPH, as this is likely to have an important impact on the application of the new knowledge and skills [32, 33].

**Table 1 Tab1:** Primary and secondary study outcomes

Primary outcome indicators	
Severe maternal morbidity	• PPH near-miss cases among all women who delivered in the facility • PPH near-miss cases among women who suffered PPH during health facility delivery • Near-miss cases among all women who delivered in the facility
Secondary outcome indicators	
Mortality (case fatality) in PPH near misses	• Deaths in PPH near-miss cases
Preventive actions and case management for PPH	• Proportion of women who received AMTSL of total women with PPH • Proportion of women with haemoglobin less than 70 g/L before discharge among those who suffered PPH • Proportion of women who received blood transfusion, intravenous oxytocin, balloon tamponade or a hysterectomy among those who suffered PPH • Proportion of women who need emergency transfer to a higher-level facility among those who suffered PPH in the health centre
Knowledge, skills and confidence in preventing and managing PPH	• Proportion of health care providers passing the knowledge test assessing preventive and emergency PPH care • Confidence score summing five questions about AMTSL, PPH, assessing advanced care, completeness of the placenta and bimanual uterine compression • Clinical skills score summing routine care including AMTSL, retained placenta and severe PPH • Team work
Facility readiness for prevention and care of PPH	• Proportion of facilities with AMTSL protocols and emergency tray available on day of visit • Proportion of facilities with at least a team of two midwives and one clinician on day of visit • Proportion of facilities with oxytocin and infusion set available in delivery room on day of visit • Stock-outs of oxytocin

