The primary outcome of this study is severe maternal morbidity defined by the WHO disease and management-based near-miss criteria and referring to women while pregnant or within 42 days of termination of pregnancy, excluding accidental or incidental cases [34]. We modified the original WHO definition criteria as proposed by Nelissen et al. [35] and supported by a recent study which indicated that restricting near misses to cases of organ dysfunctions excludes many severe cases, even in high-income settings like the Netherlands [36]. Thus we defined a near-miss case as a woman experiencing either eclampsia, sepsis or uterus rupture OR any organ dysfunction using the standard near-miss definitions OR having received blood transfusion or a hysterectomy. The indicators are constructed using the total number of deliveries reported by the facilities (indicators one and two). For indicator three ‘PPH-related near-miss cases among women who suffered PPH in health facility delivery’ we use the number of women experiencing PPH in the facility as the denominator. We measure case fatality in PPH near misses as a secondary outcome. Also, several secondary outcomes are selected to reflect knowledge and management along the pathway of implementation including equipment availability and supplies.

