### Randomisation

We use unblinded matched-pair randomisation of districts (clusters), which is done separately in each country. Criteria for matching were health care organisation (number of hospitals and health centres), urban/rural district, geographical area and a balance in the outcome measurement ‘PPH-related near-miss cases among women who suffered PPH’ available from the baseline data collection. Randomisation is done using Stata by the trial statistician, who is otherwise not involved in the study implementation. Blinding of participants is not possible due to the nature of the intervention.

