### Limitations

The main limitation of the study is that primary and secondary outcome measurements are not collected by external staff. We decided to use facility staff for several reasons: firstly ,we estimated that the time spent on collecting data in facilities would take less than 1 hour per day, which makes it unnecessary to employ external staff (and this would greatly increase costs); secondly, we received advice from local collaborators and district managers that the acceptability of external data collectors might be limited over such a long period of time; and thirdly, even if external data collectors were used, they would still rely on case notes prepared by maternity staff who are, by the nature of such a training intervention, not independent.

In order to address this, we aim to standardise the data collection during the 6-month period prior to the randomisation to reduce the reporting bias potentially introduced by the lack of blinding. In addition, our supervision team will visit the facilities every 1–3 months to verify the data by checking the registries. We also include an external assessment by independent data collectors in a sample of facilities to investigate any recording bias and confirm data completeness.

Another limitation is that the HMS training itself might improve recognition of PPH complications and recording of management. Such an unexpected reverse effect was observed in the evaluation of the Helping Babies Breathe training in Tanzania [11].

Contamination is a major threat to our evaluation. Other training or skill-building approaches in the field of safe motherhood or emergency obstetric care provided by the ministries of health or development partners might contaminate the training approach in our intervention and comparison districts. We are not able to restrict these much-needed development initiatives, as this would be unethical, but we document this when it occurs so that we are able to adjust for it in our analysis. Contamination and overall health sector development has been described in several trials to improve maternal and child health as a potential reason why results were missed [43, 44].

Finally, it is common practice that health workers are transferred to other facilities. In response, facilities in intervention districts might lose trained staff while facilities in comparison districts might then have health workers with improved skills to manage PPH.

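### One of three primary indicators divides PPH near misses by recorded PPH, a post-randomisation count that the training can move, so the ratio can be biased in either direction

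*Protocol article*

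**What the plan says.** Under Evaluation methodology, Table 1 gives three primary indicators of severe maternal morbidity. Two are per delivery, the first being "PPH near-miss cases among all women who delivered in the facility". The other is "PPH near-miss cases among women who suffered PPH during health facility delivery". The text below the table confirms its denominator: "we use the number of women experiencing PPH in the facility as the denominator". (The text calls this indicator three, while the table lists it second.) No order of precedence is stated.

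All four case-management secondaries in Table 1 also have women with PPH as denominator, for example "Proportion of women who received AMTSL of total women with PPH".

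The section on the intervention says that the training teaches blood-loss measurement, checking of uterine tone and active management of the third stage of labour (AMTSL). The Background says that it is meant both to prevent and to treat PPH. The data-collection section has every haemorrhage captured, however mild. The Limitations concede the recognition effect: "Another limitation is that the HMS training itself might improve recognition of PPH complications and recording of management". They do not connect it to this indicator.

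**The concern.** During follow-up only the intervention districts are trained. Two consequences of the training act on the denominator in opposite directions. Better measurement of blood loss can bring mild cases into the record, which raises it. Effective prevention lowers it. Either way, the women counted as having PPH in the two arms are selected differently after randomisation, and the ratio compares groups that randomisation did not make alike.

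A listed primary indicator could then show a benefit that comes from recording alone, or show none when prevention has worked. Because the article does not rank the three primary indicators, nothing in it tells the reader which result to believe if they disagree.

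**Working it through.** **Inputs.** From the Sample size section: 3000 deliveries per cluster, PPH near misses at 2% of deliveries, a 25% reduction, coefficient of variation k = 0.15, and 10 clusters per group. From the Background: "Between 11% and 17% of women who give birth in eastern Africa experience PPH", used here only to set the starting level. The size of any shift in recorded PPH is assumed.

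**1. The plan's own figure.** c = 2 + (1.96 + 0.84)² × [0.02×0.98/3000 + 0.015×0.985/3000 + 0.15²×(0.02² + 0.015²)] / (0.02 − 0.015)² = 10.003, against the stated 10. This calculation is for the per-delivery rate. The article gives none for the ratio among women with PPH.

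**2. How the two indicators respond.** Let the training multiply PPH near misses by a and recorded PPH by b. The per-delivery risk ratio (RR) is a. The RR for the ratio among women with PPH is a/b. It does not depend on the starting incidence.

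**3. Numbers for one cluster.** Near misses: 3000 × 0.02 = 60. PPH at 11%: 330. Starting ratio: 60/330 = 18.2% (at 17% it would be 60/510 = 11.8%).

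| Scenario (assumed) | Near misses | Recorded PPH | Ratio | RR, ratio | RR, per delivery |
|---|---|---|---|---|---|
| Recognition only: PPH up one third | 60 | 440 | 13.6% | 0.75 | 1.00 |
| Prevention: both down 25% | 45 | 247.5 | 18.2% | 1.00 | 0.75 |
| Mainly mild cases prevented: PPH down 40%, near misses down 25% | 45 | 198 | 22.7% | 1.25 | 0.75 |

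Smaller and larger recognition shifts scale as 1/b: a rise of 10%, 25% or 50% gives RR 0.91, 0.80 or 0.67.

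**4. Does difference-in-differences remove it?** Put 18.2% in both arms at baseline and in the comparison arm afterwards, and 13.6% in the intervention arm afterwards. The estimate is (13.6 − 18.2) − (18.2 − 18.2), about −4.5 percentage points before rounding. The whole artefact stays, because it starts after training and in one arm only.

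**5. Chance of a significant false benefit.** Use the plan's variance form with 10 clusters per group, and assume that k = 0.15 also applies to this ratio. For the one-third rise, v = [0.1818×0.8182/330 + 0.1364×0.8636/440 + 0.15²×(0.1818² + 0.1364²)]/8 = 0.000235, so √v = 0.0153. The chance is Φ(0.0455/0.0153 − 1.96) ≈ 0.84. The same formula gives about 0.64 for a 25% rise and 0.17 for a 10% rise. Starting from 17% PPH instead of 11%, the three values are 0.83, 0.63 and 0.17.

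**The case against.** The strongest reply is that PPH near misses per delivery is already listed first and carries the 10-cluster calculation. In the recognition scenario it stays at 1.00 and exposes the artefact. In the prevention scenario it shows 0.75. Read together, the two rates can help to separate prevention from progression after bleeding has begun. This stands, and it limits the harm. It is also an argument for using the ratio as an explanatory measure and not as a primary one.

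Safeguards exist. Data collectors in all facilities were trained on the definition of PPH and retrained after 5 months, recording is standardised for 6 months before randomisation, and an external team re-abstracts records in one third of facilities. These narrow the room for differential recording. They do not close it: they check completeness against registers and notes, and the Limitations accept that those notes are written by staff who are not independent. Nor can they undo a true fall in PPH.

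The magnitude is assumed, and the illustration holds the near-miss count fixed. That count includes transfusion and hysterectomy, so training could move it as well, and the net direction is unknown. This stands too. It is why the point is bias in either direction and not a predicted false benefit.

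**Conclusion.** The point holds for one of the three primary indicators. Its between-arm comparison conditions on a count that the intervention may raise or lower after randomisation. A one-third rise in recorded PPH would by itself reproduce the 25% design effect, and a proportional prevention effect would be invisible. Both rest on assumed shifts, with near misses at 2% and PPH at 11% of deliveries. The case-management secondaries share the denominator. AMTSL among women with PPH conditions on the event that AMTSL is meant to prevent; the article does not call it coverage, but a reader might.

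Three stronger readings are tempting and not supported:
- That the training also distorts the matching. The matching criterion is "a balance in the outcome measurement ‘PPH-related near-miss cases among women who suffered PPH’ available from the baseline data collection", and baseline precedes both randomisation and training, so the training cannot alter it.
- That the 11% to 17% in the Background shows how far recording could shift. It is a range of incidence and says nothing about change in recording.
- That the trial's primary result as a whole is compromised. The two per-delivery indicators do not have this denominator problem.

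**What to change.** - Keep PPH near misses per facility delivery as the primary PPH indicator, and say that it takes precedence.
- Move the ratio among women with PPH to secondary or explanatory status.
- Beside the ratio, report recorded PPH per delivery by arm and by period (baseline, follow-up), so that any movement in the denominator is visible.
- Attach the same caveat to the case-management secondaries with a PPH denominator, including AMTSL among PPH cases. Where these are also given per delivery, note that the problem is only partly solved. Discharge haemoglobin is collected for women with haemorrhage or transfusion, and treatment counts likewise depend partly on recognition.

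The change is to the outcome table and the analysis text, and should be recorded before any between-arm comparison is run. Delivery counts and case data are already collected and the sample size is unaffected. The small downside is one fewer primary indicator.

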### The intervention

The HMS BAB training is a competency-based training package developed by Jhpiego and Laerdal Global Health. The training programme has been designed to improve the knowledge and performance of delivery care providers through (1) an educational environment at the health facility level, with training conducted in health facilities; (2) an improved clinical practice environment, with material for practicing simulations provided in labour rooms; (3) monitoring quality improvement through ongoing data collection and feed-back analysis reports [30].

The training is provided by Jhpiego-accredited HMS BAB master trainers and is conceptualised to be relevant to all cadres of maternal care providers. The training lasts for approximately 4–6 h and is scheduled around the daily work of the staff. The curriculum includes theoretical and practical aspects of care, supported by pictorial flip-charts and MamaNatalie® birthing simulators, low-cost birthing simulators that can create normal and complex birthing scenarios. The birthing simulators are left in the facility after the training. The one-day training is followed by 8 weeks of in-service practice facilitated by clinical mentors. These mentors receive an additional half-day of training to guide the 8 subsequent weeks of peer practising using the MamaNatalie® birthing simulators. Mentors are supposed to organise and support these ‘low-dose, high-frequency’ weekly practice sessions which are anticipated to last 15–20 min each.

The curriculum of the main training includes (1) communication between staff and the mother, (2) preparation for a clean and safe delivery, (3) measuring blood loss, (4) checking the uterus tone postpartum, (5) routine care for mother and baby, (6) Active Management of the Third Stage of Labour (AMTSL), (7) cord cutting, (8) placenta delivery, (9) checking the placenta for completeness, (10) decision making and organisation of referral in case of complications, (11) assessment of tears as a cause of bleeding and (12) bimanual compression of the uterus. Much emphasis is placed on highlighting the provision of good care for the mother and the baby, thus the training links to the Helping Babies Breathe training. The curriculum does not cover more advanced emergency obstetric care interventions like manual removal of the placenta, balloon tamponade or surgical care.

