### Sample size

We estimate six cases of near miss per 100 deliveries of which two will be PPH-related. This cautious assumption is based on studies from Africa where the PPH-related near misses per 100 deliveries ranged from 2% in a rural referral hospital in Tanzania [35], to 5% in Zimbabwe and Zambia [38], and 9% at a tertiary hospital level in Nigeria [39]. This range is broadly supported by a recent systematic review of severe maternal morbidity in sub-Saharan Africa [6].

We assumed that the training would reduce severe morbidity (defined as near miss) by 25%. This estimate was chosen because similar training had an effect on neonatal mortality of a similar size [11]. Secondly, it has been shown that consistent use of AMTSL should reduce severe outcomes by half [40]. Other interventions included in the training, such as prompt identification of haemorrhage and immediate treatment with oxytocin, should further reduce severe outcomes [7]; thus a reduction of 25% was deemed to be possible.

We used the formula proposed by Hayes and Moulton for matched clusters [41] to calculate the number of clusters needed in order to obtain a power of 80% in our analysis. Considering the estimated coefficient of variation of near misses between clusters, we estimate that the intervention will reduce overall near misses and PPH near misses per 100 deliveries by 25% in the intervention compared to comparison clusters (districts). Anticipating 3000 deliveries in each cluster (hospital and health centres), the following formula was used:$$ \mathrm{c}=2+{\left({\mathrm{z}}_{\alpha /2}+{\mathrm{z}}_{\beta}\right)}^2\;\mathrm{x}\;\left[{\mathrm{p}}_0\left(1-{\mathrm{p}}_0\right)/\mathrm{n}+{\mathrm{p}}_1\left(1-{\mathrm{p}}_1\right)/\mathrm{n}+{\mathrm{k}}^2\left({{\mathrm{p}}_0}^2+{{\mathrm{p}}_1}^2\right)\;\right]/{\left({\mathrm{p}}_0-{\mathrm{p}}_1\right)}^2 $$

where z_α_/2 + z_β_ = (1.96 + 0.84) assuming a power of 80% and 5% error.

Considering the prevalence of near-miss haemorrhage equal to 2% in the comparison group, and assuming a *k* (the coefficient of the variation of the proportion of near misses between clusters) value of 0.15 [42], we calculated that the required number of clusters required is equal to 10 per group.
*p*
_0_ = 0.02
*p*
_1_ = 0.015 (reduction of 25%)
*n* = 3000 deliveries in a cluster
*k* = 0.15

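### One secondary indicator pools intravenous oxytocin with transfusion, balloon tamponade and hysterectomy, so it can hide a fall in severe interventions or simply track oxytocin use

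*Protocol article*

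**What the plan says.** Table 1, under preventive actions and case management for PPH, gives the indicator as "Proportion of women who received blood transfusion, intravenous oxytocin, balloon tamponade or a hysterectomy among those who suffered PPH". It is one bullet, with one numerator joined by 'or' and one denominator. The other indicators in that row have their own bullets.

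Three other places bear on how it should behave:

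- **Evaluation methodology** defines a near miss by certain diagnoses, by organ dysfunction, "OR having received blood transfusion or a hysterectomy". Either treatment alone is sufficient. One of the primary indicators in Table 1 is "PPH near-miss cases among women who suffered PPH during health facility delivery", which also has women with PPH as its denominator.
- **Sample size** assumes a 25% reduction in near misses and gives as part of the reason: "Other interventions included in the training, such as prompt identification of haemorrhage and immediate treatment with oxytocin, should further reduce severe outcomes".
- **The intervention** states: "The curriculum does not cover more advanced emergency obstetric care interventions like manual removal of the placenta, balloon tamponade or surgical care".

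Analytical methods says that secondary endpoints on management practices are analysed in the same way as the main outcome. The article states no direction of benefit for this indicator.

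**The concern.** The numerator mixes two kinds of event. Intravenous oxytocin is a treatment that the training is meant to promote. Transfusion and hysterectomy are events that the primary outcome counts as severe morbidity and that the training is meant to make less frequent. A transfused woman with PPH is thus a failure in the primary outcome and a recipient of case management in this secondary one, over the same PPH denominator.

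If training works as intended, the parts pull in opposite directions and a fall in severe interventions can disappear in the total. The row heading does not settle how to read a change, because the same row holds a good-practice item (AMTSL) beside an adverse one (haemoglobin below 70 g/L).

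What is at stake is the pathway evaluation. The Discussion relies on it to suggest explanations if the trial shows no effect, and this is the only bullet in the table that describes which PPH treatments women received.

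**Working it through.** The article gives no expected value for this indicator, so there is no stated figure to reproduce. The check asks how far the pooled proportion would move under the protocol's own effect assumption.

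**Inputs**

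- Severe haemorrhage cases: 2 per 100 deliveries (PPH near miss, Sample size). The Background gives 30 severe morbidities from haemorrhage per 1000 women, which is 3 per 100.
- PPH: 11 to 17 per 100 women giving birth (Background, a regional figure).
- Effect: 25% reduction (Sample size).
- Oxytocin use among women with PPH: not given. 70% and 90% are assumptions.
- Tamponade: no rate is given, so it is left out.

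**Step 1. Severe share of PPH cases.** s0 = severe rate / PPH rate, and s1 = 0.75 × s0. This assumes that PPH incidence itself does not change.

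| Severe per 100 | PPH per 100 | s0 | s1 | Fall (points) |
|---|---|---|---|---|
| 2 | 17 | 11.8% | 8.8% | 2.9 |
| 2 | 11 | 18.2% | 13.6% | 4.5 |
| 3 | 17 | 17.6% | 13.2% | 4.4 |
| 3 | 11 | 27.3% | 20.5% | 6.8 |

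The share is about 12% to 27% and the fall about 3 to 7 points. It stands in for the transfusion and hysterectomy share. The true share would be smaller where some near misses qualify on organ dysfunction alone.

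**Step 2. Pooled proportion if oxytocin (o) and severe interventions (s) are independent.** C = 1 − (1 − o)(1 − s). With oxytocin use constant, the change in C is −(1 − o)(s0 − s1).

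- 2 per 100, PPH 11%, o fixed at 90%: C goes from 1 − 0.10 × 0.818 = 91.8% to 1 − 0.10 × 0.864 = 91.4%. A 4.5-point fall shows as about half a point.
- Same rates, o rising from 70% to 80%: C goes from 1 − 0.30 × 0.818 = 75.5% to 1 − 0.20 × 0.864 = 82.7%. The indicator rises although severe interventions fell.

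**Step 3. Oxytocin use that cancels the whole 25% cut.** Setting C equal before and after gives o1 = 1 − (1 − o0)(1 − s0)/(1 − s1).

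| Severe / PPH per 100 | (1 − s0)/(1 − s1) | o1 from 70% | o1 from 90% |
|---|---|---|---|
| 2 / 17 | 0.968 | 71.0% | 90.3% |
| 2 / 11 | 0.947 | 71.6% | 90.5% |
| 3 / 17 | 0.949 | 71.5% | 90.5% |
| 3 / 11 | 0.914 | 72.6% | 90.9% |

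**Step 4. Full overlap.** If every woman with a severe intervention also receives oxytocin, C = o. The pooled proportion is then the oxytocin percentage and says nothing about the other three treatments.

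**The case against.** Four arguments deserve weight.

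*Four proportions may have been meant.* Table 1 is condensed, and the bullet could be shorthand for four proportions with a shared denominator, with component reporting left to the analysis plan. That is possible. But the text writes one proportion, and a definition that the article itself states can be faulted as stated. If four were meant, the correction is the same.

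*Opposite directions are only partly documented.* The protocol assumes that near misses fall, and does not predict each treatment separately. The curriculum covers decisions on referral, and Limitations concedes that training may improve recognition and recording, so recorded transfusion could even rise. This stands. It makes the expected direction of the total less clear, which favours separating the parts.

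*It is one secondary bullet among many.* A reader might infer that the pathway evaluation hinges on it. The article does not support that: AMTSL, haemoglobin, transfer, skills, confidence and readiness indicators are also listed, and nothing calls this the main process measure.

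*The primary definition is justified.* A reader might infer that transfusion should not define a near miss. Evaluation methodology gives a reason for the broader definition (restriction to organ dysfunction misses many severe cases), and Limitations discloses the recognition and recording bias. The primary definition is therefore not faulted here.

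**Conclusion.** The point holds for the indicator as written. It combines a treatment that the training promotes with events that the primary outcome treats as severe morbidity, and a change in it is a poor guide to whether PPH treatment improved.

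On the article's figures the severe share of PPH cases is about 12% to 27%, and the planned 25% cut moves it by about 3 to 7 points. This rests on regional PPH incidence, on an unchanged number of PPH cases, and on near misses or severe morbidity standing in for transfusion and hysterectomy. Every statement about offset rests on assumed oxytocin use and, in Steps 2 and 3, on independence.

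Two stronger readings are not supported. One is that the fall is at most 3 to 4.5 points: this uses only the 2% planning rate, which the protocol calls cautious, whereas the Background's 30 per 1000 gives 4.4 to 6.8. The other is that the indicator has no interpretable direction at all: where nearly all severely treated women also receive oxytocin, it simply follows oxytocin use, which can be interpreted but is not what the label says. Sample size and primary inference are untouched.

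**What to change.** Replace the bullet with separate proportions, all among women with PPH:

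- intravenous oxytocin, as a process indicator expected to rise;
- transfusion, balloon tamponade and hysterectomy, as escalation indicators.

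State for each how a rise or fall will be read, and note that transfusion and hysterectomy overlap with the primary outcome. Keep the PPH denominator. Moving the escalation indicators to all deliveries would largely duplicate the primary indicator of PPH near misses among all women who delivered.

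A sensitivity analysis of the primary outcome without women who qualify by transfusion alone is an optional addition. It would have fewer events.

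The cost is a few more secondary lines and a wording change, best dated before outcomes are compared by arm. The data form is not reproduced in the article, so the sponsor should confirm that the four treatments are recorded as separate items.
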